#### Aim 4: To examine the multi-level contextual mechanisms and factors influencing CHW effectiveness, reach, and implementation of CRC screening uptake and CAP activities.

Guided by a racism-conscious adaptation of the Consolidated Framework for Implementation Research (CFIR),^16,17^ we will conduct a mixed methods process evaluation with key stakeholders to understand multi-level influences on CRC screening and CVD risk behaviors. This information will inform future dissemination and scale-up of this intervention.

### Trial Design {8}

We will use a hybrid type 1 effectiveness-implementation design^18^ and a community based participatory research approach (CBPR)^19^ to engage AA churches and study participants. We will conduct a two-arm, cluster RCT in 22 AA churches comparing the effectiveness of CHW-delivered SBIRT (n=11 churches) to RAU (n=11 churches) on CRC screening uptake (colonoscopy, stool-based test) (primary outcome) (Figure 1). We will also examine the effect of an evidence-based CAP program incorporated into the intervention arm on DIS and on changes to CVD risk captured by LS7 scores (secondary outcomes). Lastly, we will utilize a concurrent, mixed-methods approach to assess cultural and contextual factors including barriers and facilitators of screening uptake and implementation in churches. The CFIR^30^ will guide our implementation and process evaluation. We will utilize an adapted version of CFIR, which incorporates a race-conscious lens^16,20^ to generate semi-structured interviews with key stakeholders.

There are 3 waves of data collection: baseline, 6 months, and 12 months; for the CAP there will be an additional 3-month baseline collection of the FFQ.

## Methods: Participants, interventions and outcomes

### Study Setting {9}

This study will be conducted in 22 AA churches throughout New York City. Churches with at least 500 active members where CHWs currently attend will be eligible. We will create an eligibility score based on estimates of how many in the church congregation are 45 years and older. Other criteria will include having an African American congregation with greater than two thirds who identify as Black. We have received letters of support from 25 churches which includes 3 buffer churches.

### Eligibility criteria {10}

#### General Eligibility for participation in RCT

General eligibility for study participation includes: (1) English-speaking; (2) self-identifying as Black; (3) Aged 45 years to 75; (4) not up to date with CRC screening; (5) working telephone; (6) can provide informed consent.

#### Eligibility for CRC Screening

Based on USPSTF guidelines, eligibility for CRC screening include: Church members not compliant with the following screening recommendations beginning at age 45 and up to age 75 are eligible: (1) High-sensitivity gFOBT or FIT every year; (2) sDNA-FIT every 1 to 3 years; (3) CT colonography every 5 years; (4) Flexible sigmoidoscopy every 5 years; (5) Flexible sigmoidoscopy every 10 years + FIT every year; (6) Colonoscopy screening every 10 years.

#### Exclusion Criteria

Screening questions include a family history of CRC or colorectal polyps. Participants who indicate they have an immediate family member who has or had colorectal cancer (i.e. father, mother, brother, or sister) will be excluded from participation in the study. These individuals will be directly referred for screening at one of the study’s partner hospitals.

### Informed consent {26a}

Upon completing the eligibility screener, a scoring algorithm programmed into REDCap will determine the participant’s eligibility for participation in the study. The research assistant administering the screener will then verify the participant’s eligibility scoring. Informed consent will be administered to eligible participants by trained research assistants (RAs) using REDCap. Informed consent will be obtained either in person directly following the screener at church lead recruitment events or prior to the scheduled baseline assessment, depending on the availability of the participant. This informed consent process will begin with a concise presentation of the key information about the research study, including a description of the study purpose and components, potential risks, and benefits of participating. During this process, potential subjects will have an opportunity to discuss the information provided and will be informed of their right to refuse to answer questions in the assessments or withdraw from the study if they choose to, without affecting their access to health services.

### Additional consent provisions for collection and use of participant data and biological specimens {26b}

A description of collection of biological specimens during point of care tests is included in the informed consent form.

## Interventions

### Explanation for the choice of comparators {6b}

This study will compare the effect of SBIRT and CAP (Intervention) to RAU (Usual Care) on guideline-concordant CRC screening uptake. SBIRT is an evidence-based approach, originally designed for people at risk of developing mental disorders,^21^ comprised of three components: (1) Screening with a validated instrument, (2) Brief Intervention, (3) Referral to Treatment. Alive! is an automated platform that includes step-by-step individualized tailoring, feedback, and weekly guidance through interactive emails focused on increasing physical activity, and improving eating patterns. In contrast, the RAU group will receive the most common form of referral from church-based screening events, which includes educational brochures, community resources, and a list of CRC screening sites.

### Intervention Description {11a}

#### Screening, Brief Intervention, and Referral to Treatment

Multiple studies have found SBIRT to be effective in increasing referral rates for mental health related treatment, and adherence to follow-up.^22–24^ Given the multi-generation trauma related to self-reported discrimination and resulting distrust of the medical system among AA populations,^25^ we decided to adapt SBIRT for CRC screening because it embraces Trauma-Informed Care (TIC).

The screening component will include items that will be adapted from the Behavioral Risk Factor and Surveillance System CRC screening tool to screen guideline adherence at baseline and 6-months.

The brief intervention component of SBIRT will be Motivational Interviewing (MI), which has been shown to be effective at improving health outcomes among AAs in church-based settings when delivered by paraprofessionals.^26^ MI is an empirically tested, person-centered, behavior change intervention designed to guide, elicit, and strengthen motivation for change.^27^ It decreases ambivalence and increases motivation for treatment. Studies of MI have found (1) an increase in CRC screening; (2) an increase in healthy eating patterns; and (3) improved CVD risk factor control among AA adults.^28–30^

CHWs will provide up to six-MI sessions over a three-month period. The exact number of sessions will vary based on participant needs. The sessions will occur in person or virtually via phone/zoom. Data will be collected on method of delivery. MI sessions will help eligible participants move through the various stages of change associated with seeking screening for CRC. In these sessions, CHWs will establish rapport through Open-ended questions, Affirmations, Reflections, and Summary statements (OARS), review reasons for non-compliance with guideline screening, and assess motivation and confidence regarding obtaining a screening test and elicit cognitive, emotional, and socio-economic-related barriers and facilitators of screening. CHWs will also work with participants to consider the ‘pros’ and ‘cons’ of screening, provide screening options for the participant based on the nature of barriers elicited from them and addressing social determinants of health (SDoH)-related needs, assess participant’s values and goals and help them link their current predisposition to screening to their goals, and summarize what was discussed in order to clarify an action plan.

The final component of SBIRT involves actual referrals for CRC screening. This begins with a determination of the individual’s health insurance status. Persons without insurance will be enrolled with the assistance of CHWs (who are certified New York State Insurance Navigators) into New York State health plans (insurance exchange or Medicaid). Individuals who are ineligible for health insurance will be referred to our network of local clinics providing CRC screening services regardless of the ability to pay. CHWs will secure a gastrointestinal (GI) clinic appointment for subjects who are guideline discordant for CRC screening within four weeks of the assessment (average appointment lag time within our referral networks). CHWs will refer subjects to our network of GI clinics based on subject preference and insurance status. They will also place a reminder call on the day before the appointment. We will be partnering with Harlem Hospital to screen participants for CRC.

#### Culturally-adapted Alive! Program (CAP)

Guided by the Ecological Validity Model, we will culturally adapt the Alive! Program - a cost-effective, lifestyle coaching web-based platform^31–34^ incorporating the transtheoretical model. Alive! is listed on the National Cancer Institute (NCI) Evidence-Based Cancer Control Program (EBCCP) with high RE-AIM (Reach, Effectiveness, Adoption, Implementation, Maintenance) scores for real-world translation. The current version of Alive! is delivered via an individualized website on a desktop or mobile platform and contains built-in assessments of baseline diet (using a modified Food Frequency Questionnaire, FFQ)^35^ and physical activity (using an adapted Block Physical Activity Questionnaire)^36^ for personalized feedback. We will adapt the fully automated program from its current 36-weeks to 12-weeks (we considered 3-month attrition rates^37^ and enhance the intensity of dosing by augmenting the program to include one-on-one lifestyle coaching with CHWs. We will also focus the program primarily on dietary behaviors by eliminating Alive!’s physical activity intervention component. Several RCTs have shown that the Alive! platform is effective at improving dietary habits, physical activity, body weight, and glycemic profile^31–33^ in a dose dependent manner, and CHWs have demonstrated their ability to support digital interventions targeting CVD.^38^

Cultural adaptation of Alive! will occur during the first 12 months of this proposal and will involve formative development and refinement of our intervention. In partnership with NutritionQuest developers, we will integrate CBPR to culturally adapt Alive! using processes that include focus groups with church members and community partners, which will inform the design and content on the web-based platform including the incorporation of motivational testimonials and spiritual messaging. For messaging, we will use an intersectional approach that accounts for heterogeneity within AA populations (e.g., age – 45-years vs 75-years - and gender differences). This will be an iterative process of changes and revisions using a feedback loop and a narrative performance scale (NPS).^39^ The NPS is a validated tool used to measure the effect narrative health messages on the behavioral intent of a targeted individual. We will utilize the Ecological Validity Model,^40^ which includes 8 elements for adaptation (language, persons, metaphors, content, context, concepts, goals, methods), allowing researchers to: (1) linguistically tailor the intervention by focusing on colloquial language and limiting medical jargon; (2) peripherally tailor the intervention by focusing on presenting materials in a manner that is culturally appealing; (3) socio-culturally tailor the intervention by contextualizing health issues in the broader social context such as structural racism and discrimination while imparting the importance of a health behavior.^41^ Specific Alive! modules for cultural targeting included: (1) the small-step recommended goals tailored to the individual’s dietary assessment results, which are recommended to participants each week; (2) “Health Notes” health education artiles that participants are expected to review weekly; and (3) infographics and media displayed to the participant on their Alive! homepage and in emails.

Participants within churches randomized to the intervention arm (SBIRT) will be enrolled into the CAP. Participants who cannot afford to modify their diets are referred to our CBO network specializing in providing healthy food to food insecure residents and computer tablets are provided by the study to participants without uninterruptible access to a web-based platform from a computer or smartphone (determined from baseline assessments). The project coordinator (PC) will be available to provide additional technical assistance even though studies of an unmodified version of Alive! have shown good functional feasibility among AA populations.^37^ Following SBIRT sessions, CHWs will introduce the CAP program. We will assess participants for food insecurity using the six-item short form food security survey.^42^ Enrollment in Alive! is supported by CHWs. This involves creating an online account using the participants name and email and completing embedded assessments. CAP will maintain the behavior change approaches in the unmodified version of the Alive! intervention, which uses information derived from assessments to personalize goals. Every week, participants will be expected to choose at least one eating goal, read two short Health Notes, complete quizzes associated with the health education material, and track parameters related to their dietary behaviors. They will earn virtual points for meeting goals redeemable for small non-monetary study incentives. CHWs will supplement each participant’s lifestyle programming with 1:1 coaching delivered in 15–30-minute sessions by telephone/zoom once-a-week for 4 weeks and every two weeks for 8-weeks. Sessions will focus on providing encouragement around small step weekly goals. Fidelity procedures similar to Aim 1 will be implemented. Eating habit assessments within Alive! will be captured by a brief FFQ modified to include foods that can increase or reduce inflammation. Alive! software is programmed to generate an inflammatory diet report in real-time for each participant from the brief FFQ. Alive! will also generate the Dietary Inflammatory Score (DIS)^43^which is based on food group intake (e.g., fruits), unlike the older Dietary Inflammatory Index (DII) which is based on nutrient intake (e.g., carbohydrates). This makes the DIS more useful for intervention studies compared to the DII.^43, 44^ Finally, we will develop a participant level ‘dashboard’ for CHWs with summarized data on lifestyle and dietary factors which will be used by CHWs to tailor their one-on-one coaching. This dashboard will be secure and HIPAA compliant.

#### Referral as Usual

Distributing cancer prevention pamphlets during organized church health fairs is a common health education approach. We will adopt a similar approach and distribute CRC brochures promoting the new CRC screening guidelines to participants randomized to Usual Care. Brochures will be distributed by CHWs to participants after baseline screening. For consistency, we will utilize one brochure from the National Cancer Institute and one from the Center for Disease Control and Prevention (CDC). CHWs will also distribute a list of local CRC screening referral sites (GI clinics) and a community resource guide to study participants. The Directory will function as a primary referral source to CRC screening. No CRC screening referrals will be made in this arm. At 6-month follow-up, participants will be asked by RAs whether they had a colonoscopy or any other screening test for CRC.

#### Criteria for discontinuing or modifying allocated interventions {11b}

There are no preplanned reasons for modifying or discontinuing the intervention.

### Strategies to improve adherence to interventions {11c}

The strategies we will utilize in this study to increase adherence are innovative in the following ways:

*Strategy of the Intervention:* MI has been shown to increase colorectal cancer screening.^45^ We employ a trauma-informed evidence-based approach utilizing MI called Screening (with a validated instrument), Brief Intervention (using Motivational Interviewing), and Referral to Treatment (SBIRT) originally designed for mental health behaviors^46^ for CRC screening and referral. CHWs in the intervention arm will utilize MI to decreases ambivalence and increases motivation for treatment.*Church-placed setting*: We adopt a “meet people where they are” approach by integrating our intervention into the church setting from where referrals will occur.*Use of CHWs:* CHWs can reduce health system mistrust and allow us to build health promotion capacity in the church and broader community.*Adaptation of Alive*!: We are culturally adapting Alive!,^32^ an existing NCI EBCCP listed web-based program to target CVD and CRC risk.

### Relevant concomitant care permitted or prohibited during the trial {11d}

There are no concomitant care permitted or prohibited during the study.

### Provisions for post-trial care {30}

This study is classified as minimal risk and therefore, there are no anticipated harm to the participants as a result of participating in this study. There are no plans for direct provision of post-trial care.

### Outcomes {12}

This cluster RCT will evaluate the impact of a CHW enhanced CRC screening intervention on screening uptake (clinic-based colonoscopy or home-based stool test) (primary outcome). The definition of screening uptake is the subject’s self-report of completing a CRC screening test plus the research team’s verification of this completion from medical records. The secondary outcomes include the effect of the CAP program on DIS and on changes to CVD risk captured by LS7 scores. Secondary outcomes will be measured using a modified Block Food Frequency Questionnaire (FFQ)^47^ and Life’s Simple 7 measure, respectively. The FFQ contains a food list of 83 food items that asks about eating habits in the past month, provide estimates of dietary intake, and rank individuals along the distribution of intake. Pictures are provided to enhance accuracy of quantification of portion sizes. The FFQ is intended for either self- or interviewer-administration and has been validated in studies.^35^ RAs will collect FFQ data at baseline, 3- and 6-months. The LS7 measure is based on 7 domains: 3 health physiological metrics (glucose, cholesterol, and blood pressure levels) and 4 health behavior-related metrics (body mass index, physical activity levels, diet quality, and cigarette smoking). Each factor is comprised of items that are rated at “ideal”, “intermediate” or “poor”, corresponding to a score of 2, 1, or 0 respectively. LS7 scores range from 0 to 14 and are calculated from the composite of the factor scores. CVD health is then classified as inadequate (0–4), average (5–9), or optimum (10–14). Achieving a greater number of ideal LS7 metrics is associated with lower risk of dying after stroke and all cause cardiovascular mortality in a dose dependent manner.^91,92^ RAs will collect LS7 measures at baseline, 6-months, and 1-year in the church with standard approaches and FDA approved validated point of care testing (POCT) devices for glucose and cholesterol.

### Participant Timeline {13}

**Table T2:** 

Participant Milestone	Month in Study											
	1	2	3	4	5	6	7	8	9	10	11	12
Engage churches												
RA conducts eligibility screener with potential participant												
Eligible participant consented												
RA conducts baseline with participant												
CHW conducts Intervention/RAU session(s) with participants												
RA conducts 3 month FFQ with participants												
Intervention participants engage in CAP												
RA conducts 6 month follow up												
RA conducts 12 month follow up												

### Sample size {14}

We will conduct a two-arm, cluster RCT in 22 Black churches. From each of these 22 churches, we will recruit 20 subjects for a total sample size of 440 subjects. Based on our prior study in which approximately 50% of AAs above age 50 years were not up-to-date with screening,^48^ we will screen at least 40 adult churchgoers aged 45 years and older per church for study eligibility (total screening = 880 subjects).

### Recruitment {15}

#### Recruitment of Community Health Workers

Certified CHWs (two from each church for a total of 44) trained through the Columbia InTOuCH program, will be recruited from our existing cohort of 212 CHWs. The Columbia InTOuCH program trains 45 CHWs per year on an ongoing basis, which will further expand our recruitment pool. Interested CHWs will be interviewed to assess their experience working with people to get screened for CRC and reasons for participating, as well as to clarify the roles and expectations of CHWs. All study CHWs (n=44) will receive an additional 18-hours of booster training sessions guided by the information-motivation-behavioral skills (IMB) model.^49^ CHWs will complete measures of knowledge (CRC and CVD), Motivation, and Behavioral Skills, including Self-Efficacy for screening and coaching activities. Experts will deliver training modules covering: (1) CRC treatment, prevention, disparities, and screening guidelines; (2) Inflammatory Diet and related CVD risk factors; (3) SBIRT procedures; (2) Alive! procedures; (3) Human Subjects protections (CITI and HIPAA).

#### Recruitment of churches and participants

Two CHWs and at least one Project Coordinator (PC) will introduce the CRC study to potential churches through informational sessions, and CRC awareness forums. CHWs will engage community members at screening events and gauge their interest in participating in the study. A QR code will be found on the study flyer that links to a Qualtrics sign-up sheet which the CHWs will administer. The form will be used to obtain participant demographic information. If the participant indicates they are interested in getting screened, the form will prompt the participant to provide their contact information, allowing a research assistant to contact them at a later time to be screened. Responses to this survey will be kept confidential. Only the principal investigators and the study staff will be able to see the results of the sign-up sheet. All data obtained from response to this form will be stored in the secure CUMC Qualtrics platform.

#### Recruitment of clergy

The CHWs and PC will present the study process and information on the semi-structured interview or focus groups to the lead pastor, and clergy members.

#### Recruitment of clinical providers

Providers will be identified from the study’s network of local GI clinics based on their capacity to provide CRC screening opportunities for study participants. The study PI and project director (PD) will connect with potential providers over email and zoom to discuss options for a partnership. Once a partnership is established, the study staff will work closely with clinical providers to develop a process for referring study patients to the hospital for CRC screenings.

## Assignment of Interventions: Allocation

### Sequence Generation {16a}

In this study, randomization will occur on the church level to reduce chances of contamination through interactions between congregants in the same church. Four churches will be randomized in Years 1; six churches in Years 2; six churches in year 3; and six churches in year 4 to reach our target sample size of 22 churches. Churches will be matched based on size (number of members) and randomized in a 1:1 ratio to either SBIRT and ALIVE! or RAU. A randomization sequence will be generated by the study statistician according to CONSORT guidelines. Randomization will occur on the church level prior to the start of screening events to allow for assignment to specific booster trainings with the CHWs. At the end of data collection, churches assigned to the RAU arm will be offered SBIRT.

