$\text{logit}(p)=\text{log}\left(\frac{p}{1-p}\right)=\beta_{0}+\beta_{1}X+\tau_{c}$ where X is a binary variable (0 for usual care and 1 for SBIRT intervention), *τ*_*c*_ is a random effect for clustering within churches, and p = prob(Y=1, CRC screening rate). The hypothesis H_0_: *β*_1_ = 0 vs H_1_: *β*_1_ = *β** will be tested with the formula for determining the total sample size.^58–61^: $n^{*}=\frac{{\left(V{\left(0\right)}^{1/2}Z_{1-\alpha /2}+V{\left(\beta^{*}\right)}^{1/2}Z_{1-\beta }\right)}^{2}}{P_{1}\beta^{*2}}\left(1+2P_{1}\delta \right)$ with $\beta^{*}=\text{log}\frac{P_{2}\left(1-P_{1}\right)}{P_{1}\left(1-P_{2}\right)}$, with $V(0)=\frac{1}{1-B}+\frac{1}{B}$, $V\left(\beta^{*}\right)=\frac{1}{1+B}+\frac{1}{\text{Bexp}\left(B^{*}\right)}$, *δ* = (*V*(0)^1/2^ + *V*(*β**)^1/2^*R*)/(*V*(0)^1/2^ + *V*(*β**)^1/2^), *R* = *v*(*β**)*B*(1 − *B*) exp(2*β**)/(*Bexp*(*β**) + (1 − *B*))^2^, where *P*_1_, *P*_2_ are the CRC screening rates of usual care and SBIRT (intervention), respectively, and B is the proportion of the sample assigned to each of two arms (B=0.5), *δ* is a small rate adjustment, when *P*_1_ < 0.2 (*δ* = 0 when *P*_1_ ≥ 0.20), adjusting for unreliability and clustering (g=1+(s-1)*icc):*n* = *n***g*/*R*_*el*_. The assumptions are: for α=0.05 (2 tailed test), 1-β=0.80 (power), *R*_*el*_ = 0.95 (adjusted for unreliability), g=1.57 (variance inflation factor adjusting for clustering), with cluster size s=20 and icc (intracluster correlation coefficient=0.03). *P*_1_ (X=0, usual care group), *P*_2_ (X=1, intervention group), B=0.5, n=total sample size, and power for n=396 (m=198 per group, about 11 churches per group with attrition rate=10% at 6 months with an average of 20 participants per church)/

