Regarding the CRC screening rate, a sample size of 198 subjects per group (10 to 12 churches per group, average of 20 subjects per church, attrition rate of 10% at 6 months) is required to provide 80% or greater power to detect a group difference of 15% (a clinically meaningful increase) in the rates of completed colorectal cancer screening at 6 months. Thus, power will be sufficient to detect the hypothesized difference from baseline in both arms. As shown above, these calculations assume a baseline rate of 0 and scenarios with increase in screening rates in the usual care group from 0.20 to 0.50. Thus, with an overall sample size of 440 subjects or 220 per arm (11 churches per arm with 20 subjects in each church), the study is powered adequately, even with attrition. Based on our prior study in which approximately 50% of AAs above age 50 years were not up to date with screening,^48^ we will screen at least 40 adult churchgoers aged 45 years and older per church for study eligibility (total screening = 880 subjects).

#### Power analysis for Aims 2 and 3

Aim 2 is to evaluate the effect of a CAP incorporated into the intervention arm on DIS at baseline and 6-month follow up; and Aim 3 is to evaluate the effect of CAP on changes in LS7 at baseline, 6-months and 12 months. Sensitivity analyses will be performed including data from the 3-month wave. Power calculations were performed for an analysis of covariance (ANCOVA)-type model: *y*_*ijk*_ = *μ*_*jk*_ + *y*_*i*0_ + *τ*_*c*_ + *e*_*ijk*_, where *μ*_*jk*_ is the group mean for follow up DIS and LS7, *y*_*i*0_ is the baseline measure, j=1,2 follow-ups and k=0, 1 for group, *τ*_*c*_ is a random effect for clustering within church. The power analysis equation for one follow-up is: $n=\frac{2{\left(z_{\alpha }+z_{\beta }\right)}^{2}\sigma^{2}\left(1-\rho^{2}\right)g}{d^{2}R_{el}}$: where *ρ* is the correlation between the outcome and baseline values, *σ* is the standard deviation, *d*_*I*_ is the follow-up difference between 2 groups, *R*_*el*_ is the reliability of the outcome, adjusting for clustering within churches, g=1+(s-1)*icc, and n is number of subjects per group.

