For the LS7 outcome, with baseline and two follow ups, it is assumed that σ=2.7 (standard deviation). Assuming the difference between the 2 groups is unequal will result in lower power than if equal. A correlation structure of compound symmetry will result in lower power than autoregressive (AR). The primary analyses assume ITT for the 3rd wave, α = 0.05 for a two-tailed test. However, effects assuming 20% attrition, with m = 176 per group at 1 year study-end were also calculated (baseline m=220, 6-month m=198 and 1 year m=176). With an m = 198 per group at 6-months (ITT model for 3rd wave), it will be possible to detect an effect size of δ=0.764 (Cohen’s d=0.283), with power of 0.80. With the correlation between baseline and follow up equal to 0.6, the Cohen’s d=0.265 (which translates to an effect size of δ=0.716). Examining different scenarios regarding the difference between the groups and the correlation structure of compound symmetry, or AR, the detectable effect sizes range from δ=0.645 (Cohen’s d=0.239) to δ=0.810 (Cohen’s d=0.300) with power of 0.80.

#### Analysis for Aim 1

Logistic-type regression analyses will be used to test the hypothesis that those assigned to SBIRT will have significantly higher CRC screening rates compared to those randomized to RAU at 6 months. Clustered sampling effects due to churches will be incorporated using a multilevel modeling approach. Ideally, the randomization of participants to treatment arm and the absence of significant selection and/or attrition biases will obviate the need for inclusion of covariates. In the event that the logit analyses indicate one or more sources of potential bias, the predicted values of those analyses will be included as covariates in a multilevel logistic regression model (SAS, PROC GLIMMIX).

#### Analysis for Aims 2 and 3

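### The Aim 1 primary model leaves out the church-size matching and the yearly randomisation sets, and lets bias tests on the trial data decide whether covariates enter

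*Protocol article*

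**What the plan says.** Sequence Generation {16a} sets the allocation: "Churches will be matched based on size (number of members) and randomized in a 1:1 ratio". It also gives the schedule: "Four churches will be randomized in Years 1; six churches in Years 2; six churches in year 3; and six churches in year 4". The same section says that allocation is at church level.

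The section on statistical methods for primary and secondary outcomes {20a} writes the Aim 1 model out as a logistic regression with an arm indicator and a random effect for church. Its Analysis for Aim 1 paragraph repeats the multilevel approach and deals only with clustering by church. On whether to adjust at all it says: "Ideally, the randomization of participants to treatment arm and the absence of significant selection and/or attrition biases will obviate the need". It then gives the exception: "In the event that the logit analyses indicate one or more sources of potential bias, the predicted values of those analyses will be included as". Those values would become adjustment terms when the primary model is fitted with PROC GLIMMIX.

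For Aims 2 and 3 the same section gives a basic model with the baseline value and arm. Further covariates and interactions may be added where needed, and variables that differ between arms are left to secondary analyses. Church size, matched set and randomisation year appear in none of the stated models or power formulas.

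**The concern.** Two things are at stake in the primary analysis.

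The first is pre-specification. Whether covariates enter, and which predicted values they are, depends on analyses of selection and attrition in the trial's own data. Attrition occurs after randomisation. The article gives no threshold or criterion for deciding that bias is indicated. A quiet imbalance test across 22 churches is also weak evidence of balance.

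The second is agreement between design and analysis. Matching on a factor that predicts the outcome makes the two arms more alike than chance would, so the true sampling variance of the arm effect falls. A model that omits the factor still counts that variance as error. The standard error is then too large, the test rejects too rarely under the null, and part of the benefit of matching is lost.

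**Working it through.** **Inputs from the article.** Test and target power: "for α=0.05 (2 tailed test), 1-β=0.80 (power". Effect: "power to detect a group difference of 15% (a clinically meaningful increase" in the screening rate. Control rates: "increase in screening rates in the usual care group from 0.20 to 0.50". Clustering: "with cluster size s=20 and icc (intracluster correlation coefficient=0.03". There are 11 churches and 198 analysed participants per arm, so 198/11 = 18 per church. Reliability is 0.95.

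**The plan's own figure.** The article's formula with B = 0.5, δ = 0, control rate 0.20 and intervention rate 0.35 gives:

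- β* = log[(0.35 × 0.80)/(0.20 × 0.65)] = 0.767
- V(0) = 4 and V(β*) = 2 + 1/(0.5 × 2.154) = 2.929
- n* = (2 × 1.960 + 1.711 × 0.842)²/(0.20 × 0.767²) = 244
- n = 244 × 1.57/0.95 = 403

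At a control rate of 0.25 the result is 398. Both are close to the stated 396. This reads the first term of V(β*) as 1/(1−B); the printed 1/(1+B) gives 348 at 0.20. The formula has no term for size or year.

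**Variance of the arm effect.** Let e be the share of between-church variance explained by size and year. The article gives no value, so e = 0, 0.3 and 0.5 are assumed. The per-church variance factor is V(e) = 0.03(1−e) + 0.97/18:

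- V(0) = 0.0839
- V(0.3) = 0.0749, which is 11% lower
- V(0.5) = 0.0689, which is 18% lower

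The standard error of the difference is √{[p₁(1−p₁) + p₂(1−p₂)] × V(e)/11}. At 20% versus 35% the bracket is 0.3875 and the standard error is 0.0544, 0.0514 or 0.0493. The noncentrality, 0.15 divided by the standard error, is 2.76, 2.92 or 3.05. At 40% versus 55% the bracket is 0.4875.

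**Matched but unadjusted.** The true variance follows V(e), but the model estimates V(0). The test therefore behaves as if its 20 df critical value of 2.086 were multiplied by √[V(0)/V(e)]:

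| e | Multiplier | Effective critical value | Type I error |
|---|---|---|---|
| 0 | 1.000 | 2.086 | 5.0% |
| 0.3 | 1.058 | 2.208 | 3.9% |
| 0.5 | 1.103 | 2.302 | 3.2% |

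**Adjusted.** Log size takes 1 df and year takes 3, leaving 20 − 4 = 16 df (critical value 2.120). Eleven matched-pair effects leave 10 df (critical value 2.228). Noncentral t power for 15 points:

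| Control rate | e | Matched, unadjusted | Size and year (16 df) | Pair effects (10 df) |
|---|---|---|---|---|
| 20% | 0 | 74.7% | 73.6% | 70.1% |
| 20% | 0.3 | 75.8% | 78.3% | 74.9% |
| 20% | 0.5 | 76.6% | 81.5% | 78.3% |
| 40% | 0 | 64.8% | 63.7% | 60.3% |
| 40% | 0.3 | 65.6% | 68.6% | 65.1% |
| 40% | 0.5 | 66.1% | 72.2% | 68.7% |

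Setting the unadjusted and 16 df powers equal gives a break-even e of about 9% at a 20% control rate and 8% at 40%. For pair effects it is about 37% and 33%. These powers leave out the 0.95 reliability factor. Including it lowers the e = 0 unadjusted figure at 20% from 74.7% to 72.5%.

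**Simulation.** In 6,000 runs of 22 churches paired on size within year, with binary outcomes at 20% versus 35%, the unadjusted test had type I error 0.051 at e = 0 and 0.038 at e = 0.3. The test adjusted for size and year had 0.050 and 0.051. Power, unadjusted versus adjusted, was 74.7% versus 72.6% at e = 0 and 75.6% versus 77.9% at e = 0.3.

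**The case against.** The strongest reply is that leaving out a balanced matching factor does not bias the comparison and errs on the safe side, while the power gain rests on a prognostic strength that nobody has stated. Both parts stand. At e = 0 adjustment costs about a point of power.

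A reader might infer a larger gain, of 3.6 to 6.8 points at a 20% control rate, by taking 74.7% as the unadjusted power throughout. That treats matching as having no effect until the model includes it. Matching has already reduced the true variance, so the fair baselines are 75.8% and 76.6%, and the gain is 2.5 to 4.9 points.

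Four other stronger readings are not supported:

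- **Aims 2 and 3.** The test-driven covariate rule is stated for Aim 1. The Aim 2 and 3 models always include the baseline value and allow other covariates where needed.
- **Year as a stratum.** The article gives the number of churches randomised each year but does not name year as a stratification factor. Balance within year is an inference.
- **Individual randomisation.** The Aim 1 paragraph speaks of randomising participants, but allocation is plainly at church level and the model carries a church effect. This is loose wording.
- **No named covariate list.** That is ordinarily left to the statistical analysis plan, which is not at hand.

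The last point does not answer the concern. The article does state a model and a covariate rule, and those are what need changing.

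**Conclusion.** The concern holds for the Aim 1 primary analysis. As written, the model omits the factor used for matching and the yearly sets, and its covariates depend on bias analyses of the trial data. The pre-specification fault needs no assumption about prognosis. Its effect on error rates cannot be calculated, because the article gives no decision criterion.

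The effect of omitting the design factors is conditional and moderate. If size and year explain 30% to 50% of between-church variance, type I error is 3.9% to 3.2%. Adjustment then adds 2.5 to 4.9 points of power at a 20% control rate and 3.0 to 6.1 points at 40%. If they explain nothing, the test keeps its 5% level and adjustment loses 1.1 points. These figures assume the article's ICC of 0.03, 18 analysed per church, and allocation balanced on size and year.

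A reader might infer that the primary comparison is biased, that false positives are inflated by omitting the design factors, or that adjustment is certain to gain power. The article supports none of these: the omission makes the test conservative, and the gain depends on unstated prognostic strength.

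**What to change.** State in advance that the primary GLIMMIX model includes log church membership and randomisation year as fixed effects beside arm and the church random effect, whatever imbalance tests show. Use the same terms in the Aim 2 and 3 Proc Mixed models, and base church-level inference on small-sample degrees of freedom for 22 churches.

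Do not use matched-pair fixed effects. They leave 10 df and give less power than the unadjusted analysis unless the pairs explain about a third or more of between-church variance.

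Move the conditional predicted-value rule to a sensitivity analysis. Any participant covariates in the primary model should be fixed in advance and be baseline measures taken in both arms. Insurance status shows why this matters: the article describes determining it within the intervention arm's referral step.

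The cost is wording, about 4 church-level degrees of freedom (critical value 2.09 to 2.12), and about 1 point of power if size and year prove not to be prognostic. Recruitment is expected to run to 2027, so the change can be made before analysis.
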